### 5.3 Treatment Arms

#### 5.3.1 Randomization to Treatment

Enrolled participants will be randomized (ratio of 1:1) at baseline using an online random number generator (Randomizer.org), to one of two treatments: (1) 10,000 lux BLT lamp, or (2) 500 lux modified BLT lamp. Randomization will be double-blinded, as neither the study personnel nor the participants will be aware of the treatment allocation. An information sheet will be provided to all participants to ensure that they are aware of the treatment plan and to provide the contact information of the study personnel. The 4 week treatment period will begin after surgery.

#### 5.3.2 Treatment

Participants in the 10,000 lux lamp group will be supplied with an electric BLT lamp emitting 10,000 lux light intensity. Participants in the 500 lux lamp group will be instructed to use the lamp for 30 minutes each morning, preferably upon waking, but not past 1:00 pm. Use will be monitored via self-

report at the day 4, day of discharge, and week 4 visits.

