| 3.3 | Route of Administration                 | 
Participants will be exposed to the light by sitting 12 inches from the lamp while looking at a surface that the light is reflecting onto. They should not look directly into the light, but may glance at it occasionally. This therapy can be done while reading, eating, or doing other seated activities.
                                                                                                                                                                                                                                                                                                                                                                                                                                                                                                                                                                                                                                                                                                  |
| 3.4 | Dose and Dosage Regimen                 | 
Participants will be instructed to use the light for 30 minutes each morning within an hour of waking, but not past 1:00 pm (to ensure that sleep does not become disturbed). The light must be approximately 12 inches from the participants' faces. Rulers will be used in hospital to ensure participants use the lamp at the proper distance. The length of time, and distance from the lamp both affect the intensity of light being received. Participants' eyes should be open when using the lamp, but they should not look directly into the lamp.
                                                                                                                                                                                                                                                                                                                                                                                                                                                    |

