| 3.5 | Product Accountability                  | 
All lamps will be blinded using blind codes. An inventory sheet listing the blind codes will be retained. The lamps will be stored in a locked cabinet inside the investigator's office. An accountability log will be kept to log dispensing of lamps to enrolled participants.
                                                                                                                                                                                                                                                                                                                                                                                                                                                                                                                                                                                                                                                                                                                               |
| 3.6 | Treatment Period                        | 
The treatment period will last 4 weeks and will begin once the participant consents to be in the study, is found to be eligible, and is randomized. The treatment will begin in-hospital and will continue at home after hospital discharge, for the remainder of the 4 weeks.
                                                                                                                                                                                                                                                                                                                                                                                                                                                                                                                                                                                                                                                                                                                                 |

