## 4. TRIAL DESIGN

### 4.1 Summary of Trial Design

We will conduct a RCT with a treatment period of 4 weeks and 12 week follow-up post-cardiac surgery. A total of 38 cardiac surgery participants will be randomized 1:1 to one of two treatment arms: 1) BLT or 2) Dim light (control group). Participants randomized to the BLT arm will receive a lamp emitting 10,000 lux light intensity, while those in the dim light arm will receive lamps emitting 500 lux. These lamps will both appear bright to participants, but only the high intensity light has been shown to be therapeutic. We will be using the TRAVelite Desk Lamp manufactured by Northern Light Technologies. Study personnel and participants will be blinded as to treatment allocation. Permutated block randomization will help ensure a balance of known and unknown confounders. Informed consent will be obtained in person from all individuals. Potential participants will be informed that the purpose of this pilot study is to assess the feasibility of carrying out a large trial to investigate BLT for depressive symptoms in cardiac surgery patients. The follow-up visits and data to be collected will be discussed, as well as alternatives to participation, issues of confidentiality, and

participants' rights and responsibilities. Potential participants will be given sufficient time to ask questions and decide whether or not to participate prior to signing and receiving a copy of the signed consent form.

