Participants will also be provided with an information sheet containing study procedures and contact information for study personnel. Participants in both groups will begin using the lamps in-hospital and will continue the treatment at home for the remainder of the 4 weeks post-surgery. At baseline, participants will complete the Patient Health Questionnaire 9 (PHQ-9), Depression Anxiety Stress Scale short version (DASS-21), and Short Form (36) Health Survey (SF-36) questionnaire in order to determine index levels of depressive symptomology (PHQ-9, DASS-21) and health-related quality of life (SF-36). A case report form, to collect demographic and clinical information, will be completed at baseline. On day 4 and on the day of discharge, participants will complete questionnaires and a CRF will be completed assessing adherence, tolerability, and side effects. There will be a clinic visit at week 4, when patients will return their lamp and complete questionnaires, and study personnel will complete a case report form to monitor treatment adherence. At week 12, participants will have the option to complete their questionnaires online or by mail. To compensate participants for expenses incurred due to participation (parking, childcare, opportunity costs, etc.), they will receive \$25 at week 4 and a \$20 prepaid VISA card after completing the questionnaires at week 12.

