4.4 Secondary Endpoints

(2) Retention rate: percentage of participants who remain in the study at week 12.

(3) Adherence rate: percentage of participants that used their lamp on  $\geq 60\%$  of mornings within an hour of waking for at least 25 minutes.

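### Section 5.3.2 splits lamp supply and use instruction between the arms, and its looser timing lets a participant follow it and still be scored non-adherent under 4.4

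*Protocol*

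**What the plan says.** Section 5.3.2 (Treatment) opens with two sentences. The first concerns the active arm and covers supply only: "Participants in the 10,000 lux lamp group will be supplied with an electric BLT lamp emitting 10,000 lux light intensity". The second concerns the 500 lux arm and covers use only; those participants are "instructed to use the lamp for 30 minutes each morning, preferably upon waking, but not past 1:00 pm".

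Other sections treat the arms alike:

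- Section 3.4 (Dose and Dosage Regimen), without distinction of arm: "Participants will be instructed to use the light for 30 minutes each morning within an hour of waking". It adds the same 1:00 pm limit.
- Section 4.1: "those in the dim light arm will receive lamps emitting 500 lux", and "Participants in both groups will begin using the lamps in-hospital".
- Section 5.3.1: "An information sheet will be provided to all participants to ensure that they are aware of the treatment plan". Staff and participants are blinded to allocation.

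Section 4.4 defines the adherence rate as the percentage of participants who used the lamp on at least 60% "of mornings within an hour of waking for at least 25 minutes". Section 3.6 sets the duration: "The treatment period will last 4 weeks".

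**The concern.** Read literally, 5.3.2 leaves the active arm without a regimen and the control arm without a lamp. Nobody is likely to act on that reading. Two parallel sentences probably lost their middle part.

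The timing is a different matter. The protocol contains two timing instructions, a firm one-hour window in 3.4 and a mere preference in 5.3.2, and the endpoint scores only the stricter one. No order of precedence is given. Section 5.3.2 sits in the procedures chapter, directly after the promise of an information sheet on the treatment plan, and the protocol does not say which timing that sheet carries.

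Adherence is a named secondary endpoint and part of the feasibility objective in 1.2, and 7.3 says it has to be assessed before a full trial. If participants are told the looser rule and scored on the stricter one, the result mixes unwillingness to use the lamp with an instruction that never asked for the scored behaviour. Analysis cannot repair an instruction already given.

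**Working it through.** The plan states no figure on this point, so there is none to reproduce. The check compares the texts and then applies the 4.4 threshold.

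**Timing rules side by side**

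| Section | Addressed to | Relation to waking | Latest time | Minutes |
|---|---|---|---|---|
| 3.4 (instruction) | all participants | within one hour, firm | 1:00 pm | 30 |
| 5.3.2 (instruction) | 500 lux arm, as written | upon waking, preferred | 1:00 pm | 30 |
| 4.4 (scoring) | all participants | within one hour, required | not stated | at least 25 |

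The 1:00 pm limit is common to both instructions. The conflict lies only in the relation to waking. Following 3.4 also satisfies 5.3.2; the reverse does not hold.

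**Mornings needed under 4.4**

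- Inputs: 4 weeks (3.6) and the 60% threshold (4.4). Assumption: all 28 mornings count in the denominator.
- 4 × 7 = 28 mornings; 0.60 × 28 = 16.8, so at least 17 must qualify (17/28 = 60.7%; 16/28 = 57.1%).

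**Late mornings that produce a non-adherent score**

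- None missed: 28 − 17 + 1 = 12. With 11 or fewer late mornings the participant is still adherent.
- With m mornings missed: 12 − m. For m = 4, 8 late mornings are enough.
- Extreme case, with an assumed waking time of 7:00 and lamp use at 10:00 every day: 28/28 mornings within the firm limit of 5.3.2, 0/28 qualifying under 4.4.

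**Effect on the adherence rate among 38 participants**

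- One participant so classed: 1/38 = 2.6 points.
- Three: 3/38 = 7.9 points, about the ±8% that 7.3 states for an 80% compliance rate.
- Five: 5/38 = 13.2 points. For comparison, the Wald half-width at 80% and n = 38 is 1.96 × √(0.8 × 0.2 / 38) = 12.7 points.

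The counts of three and five are illustrations of scale. The protocol gives nothing from which to derive how many participants would be late that often.

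**The case against.** The strongest reply is that 3.4 is the dedicated dosing section, covers everyone and agrees with 4.4, while 5.3.2 is a short restatement. A participant who follows 3.4 satisfies all three sections, so harm arises only if staff use the looser text. That is right as far as it goes, and it is why the point is minor. It does not remove the conflict: the protocol does not rank the sections, and 5.3.2 is the one that describes what is done with participants.

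A second reply is that someone late on 12 of 28 mornings has disregarded a stated preference and is scored correctly against 4.4 as defined. This is partly fair. The score is a true value of the defined endpoint. But a preference is not a requirement, and under the 5.3.2 wording the low score would partly reflect the instruction.

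Third, the split between arms has no practical consequence, because the intent is plain from 3.4, 4.1 and 5.3.1. This stands. A line lost when the PDF was read cannot be wholly excluded either, though both sentences are complete and grammatical.

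Fourth, the information sheet is not available for review, and a protocol need not say which sentence is copied onto it. This also stands: checking the sheet is advice, and its content is not a defect shown here.

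**Conclusion.** The concern holds, at minor severity. Section 5.3.2 is wrong as written on which arm gets what, and its timing conflicts with 3.4 and 4.4. A participant told only the 5.3.2 wording can keep to its firm limit every day and be counted non-adherent after 12 late mornings out of 28, or fewer if some mornings are missed.

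The direction is towards lower measured adherence, by 2.6 points per affected participant. The expected total is unknown, and it is zero if 3.4 is used throughout. Because allocation is blinded, either wording would reach both arms alike, so no between-arm difference or unblinding is expected. The primary endpoint, recruitment rate, is not affected.

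The textual mismatch is certain. Any effect on the result depends on which wording reaches participants. The morning counts assume a 28-morning denominator.

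**What to change.** Replace the first two sentences of 5.3.2 with one statement covering both arms: each participant receives one lamp, 10,000 or 500 lux by allocation, and all get the 3.4 regimen, that is, 30 minutes daily, no later than one hour after waking and never after 1:00 pm. Check that the information sheet gives the same timing, so that 4.4 scores the instruction participants actually received.

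The cost is two sentences in the protocol and a wording check of the sheet. Sample size, visits and procedures do not change.

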#### 5.4 Follow-Up

##### 5.4.1 Duration of Participation

Study participation begins once eligibility and consent have been established and continues until one of the following events occurs: (1) the week 12 questionnaires have been completed; (2) the participant withdraws his or her consent; or (3) the participant is lost-to-follow-up and the window for week 12 has closed. A study termination form will be completed for each participant when their study participation ends. Participants will complete a clinic visit on day 4, day of discharge, and at week 4, and will complete questionnaires via distance (online or by mail) at week 12.

##### 5.4.2 Data Collection

A case report form (CRF) will be completed at baseline, day 4, day of discharge, and week 4. At week 12, participants will complete a survey to provide additional data. At baseline, the CRF will collect demographic and clinical information, including medical history, current medications, surgery details, and depression history. Participants will also complete three questionnaires: SF-36, PHQ-9, and DASS-21. At day 4, day of discharge, and week 4, participants will be asked about protocol adherence, symptoms, and AEs or SAEs. They will also complete the same three questionnaires to assess depressive symptoms and health-related quality of life. At week 12, participants will be asked to complete these same questionnaires as well as a survey assessing symptoms via distance either through mail or an online questionnaire website. During enrollment, participants will be asked about their preference (i.e. mail or online). If they choose the mail option, the questionnaires will be mailed to their address, along with a return envelope and stamp. If they choose the online option, they will be sent an email at week 12. The email will contain a link to the online survey (SurveyMonkey), which they can use to access the survey and complete the questionnaire.

##### 5.4.3 Source Data

All data collected at baseline and follow-up visits on CRFs and questionnaires will be considered source data. Medical records will also be considered source data.

##### 5.4.4 Schedule of Events

| Visit            | Window  | Visit Type | CRF | Questionnaires        |
|------------------|---------|------------|-----|-----------------------|
| Baseline         | N/A     | In-Person  | Yes | PHQ-9, SF-36, DASS-21 |
| Day 4            | ± 1 day | In-Person  | Yes | PHQ-9, SF-36, DASS-21 |
| Day of discharge | ± 1 day | In-Person  | Yes | PHQ-9, SF-36, DASS-21 |

|         |          |              |     |                                                  |
|---------|----------|--------------|-----|--------------------------------------------------|
| Week 4  | ± 7 days | In-Person    | Yes | PHQ-9, SF-36, DASS-21                            |
| Week 12 | ± 7 days | Via Distance | No  | PHQ-9, SF-36, DASS-21, survey assessing symptoms |

5.4.5 Loss to Follow-up

Participants will be returning to the clinic for a post-operative medical appointment 4 weeks after their surgery. Their week 4 study visit will be scheduled for the same day, to help ensure participants' presence. At baseline, we will obtain contact information (email addresses, phone numbers, and addresses) for each participant as well as for at least one other individual who does not reside with the participant, to ensure that we will still be able to get in touch with participants if their phone numbers or addresses change. Finally, the commitment required for week 12 is minimal and participants will be compensated for their time. To minimize the amount of missing data due to loss to

[figure not shown]

follow up, we will use the flow chart depicted below to collect as much data as possible for each participant.

5.4.6 Participant Withdrawal

Participants may withdraw at any time from the trial. A reason for withdrawal will be solicited from participants if possible. If the withdrawal is requested during the treatment period, participants will be requested to return the investigational product (lamp) to the study centre. No negative

consequences are anticipated from abrupt discontinuation of the investigational product. Data collected up to the point of withdrawal will be retained in the study database and used in analyses. Withdrawn participants will not be replaced.

#### 5.4.7 Confidentiality

All information obtained from research participants will be treated confidentially within the limits of the law. No information that discloses the identity of participants will leave the enrolling institution. Other information will be coded and kept on a secure computer server at the Jewish General Hospital (Montreal, QC). All study information will be kept for a minimum of 25 years, under the responsibility of the principal investigator.

Unless specific authorization is provided by the participant, or where the law permits or a court order has been obtained, participant data will not be made available to third parties such as employers, governmental organizations, insurance companies or educational institutions. This also applies to the participant's spouse, other family members, or the participant's physician. However, for the purposes of ensuring the proper management of the research, a member of an ethics committee, a Health Canada representative or the study sponsor (Jewish General Hospital, Montreal QC) or its monitoring agents and representatives, may review participant research data as well as participant medical records for the purpose of monitoring this research.

## 6. TRIAL SAFETY

### 6.1 Collection of Safety Data

We will collect data regarding AEs, SAEs, and investigational product tolerability from participants at day 4, day of discharge, and weeks 4 and 12. All BLT lamps will be cleaned and sterilized before being given to participants, as well as when participants leave the hospital, to prevent possible spread of infection and reduce contamination concerns.

### 6.2 Adverse Events

An AE is any unfavourable and unintended sign, symptom, or disease temporally associated with the use of the trial product, whether or not considered related to the trial product. Study personnel will collect information concerning AEs at all follow-ups. Participants who experience AEs which may be related to the investigational product will be advised to contact study personnel concerning new or worsening symptoms. Study personnel will continue to assess AEs throughout the follow-up period.

### 6.3 Serious Adverse Events

A SAE is an AE that requires in-patient hospitalization or prolongation of existing hospitalization, that causes congenital malformation, that results in persistent or significant disability or incapacity, that is life threatening, or that results in death. Any other significant clinical event, not falling into the criteria above, but which in the opinion of the investigator requires reporting, may also be considered a SAE. If a SAE occurs, the investigator will gather any further documentation as needed (e.g., hospital discharge summaries, etc.). All SAEs will be reported to the Institutional Review Board (IRB). In the case of serious expected and/or unexpected suspected adverse reactions (SUSARs), Health Canada will be notified within 8 days of the event.

## 6.4 Unblinding

While unlikely, the investigator can decide whether or not to unblind a participant due to an AE or SAE. Participants can be unblinded by an authorized individual.

## 7. DATA ANALYSES

### 7.1 Description of Analyses

The primary analyses will describe the outcomes. The initial descriptive analysis will examine the balance of demographic variables between the 2 treatment groups. Due to randomization, known and unknown confounders should be equally distributed among the participants in the two treatment arms. Discrete data will be described using proportions. Continuous data will be described using means and standard deviations or, in the presence of skewed distributions, medians and inter-quartile ranges. These analyses will determine the recruitment rate, retention rate, protocol adherence rate, as well as process time needed. Finally, potential challenges, and important data values not collected will be assessed.

### 7.3 Sample Size Justification

The sample size of 38 participants (19 per arm) was chosen in order to appropriately test the study procedure and methods within the available timeframe. Acceptability and adherence to the intervention must be assessed before conducting a full trial. A sample size of 19 participants per arm should be able to demonstrate the ability to execute the specific protocol. If 100 eligible patients are identified, we will be able to estimate a participation rate of 38% to within a 95% Confidence Interval (CI) of +/- 7%. Additionally, with a sample size of 38, we will be able to estimate a compliance rate of 80% to within a 95% CI of +/- 8%.

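### Both precision figures in the sample size justification are wrong: the 95% half-widths are about 9.5 and 12.7 percentage points, not 7 and 8

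*Protocol*

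**What the plan says.** Protocol section 7.3 states the size and then what it delivers. "The sample size of 38 participants (19 per arm) was chosen" so that procedures could be tried out in the time available; two precision statements follow.

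- Participation: "If 100 eligible patients are identified", then "we will be able to estimate a participation rate of 38% to within a 95% Confidence Interval (CI) of +/- 7" percent.
- Compliance: "with a sample size of 38, we will be able to estimate a compliance rate of 80% to within a 95% CI of +/- 8" percent.

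Each statement gives the rate, the denominator, the confidence level and the half-width. Section 7.3 names no interval method, finite-population correction or other confidence level. Section 4.1 agrees on the total ("A total of 38 cardiac surgery participants will be randomized 1:1"), and section 5.4.6 adds "Withdrawn participants will not be replaced", so the compliance denominator can be at most 38.

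**The concern.** The half-width of a 95% interval for a proportion is fixed, to within small differences between methods, by the rate and the denominator. A rate near 40% from 100 people is known to within about 10 points. A rate of 80% from 38 people is known to somewhat worse than that. Half-widths of 7 and 8 points look too small on sight, and the second is the more striking because its denominator is much smaller.

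These are the only precision figures in the justification, and both err in the favourable direction. The pilot's purpose is to judge whether a full trial is feasible. Recruitment rate is its single primary endpoint (section 4.3), and adherence is a secondary endpoint (section 4.4). Anyone relying on section 7.3 would expect the pilot to pin these rates down more tightly than it can.

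**Working it through.** **Inputs, all from Protocol section 7.3.** Participation: p = 0.38, n = 100, stated half-width 0.07. Compliance: p = 0.80, n = 38, stated half-width 0.08. Confidence is 95% for both, so z = 1.96.

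**Step 1: try to reproduce the stated figures.** Half-width = z × √(p(1 − p)/n).

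- Participation: √(0.38 × 0.62/100) = 0.0485; 1.96 × 0.0485 = 0.095, or 9.5 points (28.5% to 47.5%). Stated: 7.
- Compliance: √(0.80 × 0.20/38) = 0.0649; 1.96 × 0.0649 = 0.127, or 12.7 points (67.3% to 92.7%). Stated: 8.

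Neither is reproduced. The ratios are 9.51/7 = 1.36 and 12.72/8 = 1.59, so the correct half-widths are 36% and 59% larger than those printed.

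**Step 2: try other interval methods.** 80% of 38 is 30.4, so for methods that need a count both 30 and 31 were used. Entries are half the interval width, in percentage points.

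| Method | 38 of 100 | 30 of 38 | 31 of 38 |
|---|---|---|---|
| Wilson | 9.35 | 12.6 | 12.1 |
| Agresti-Coull | 9.4 | 12.9 | 12.4 |
| Jeffreys | 9.4 | 12.7 | 12.1 |
| Exact (Clopper-Pearson) | 9.9 | 13.9 | 13.3 |
| Stated in section 7.3 | 7 | 8 | 8 |

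A continuity correction to the normal formula widens the intervals further, to 10.0 and 14.0 points. The exact intervals are about 28% to 48% for 38/100, 63% to 90% for 30/38 and 66% to 92% for 31/38.

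**Step 3: ask what would produce the stated figures.**

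- *A lower confidence level.* The implied z is 0.07/0.0485 = 1.44 for participation, which is about 85% confidence, and 0.08/0.0649 = 1.23 for compliance, about 78%. Even a 90% interval gives 8.0 and 10.7 points.
- *A finite-population correction.* Treating the 38 as drawn from 100 gives 12.7 × √(62/99) = 10.1 points for compliance, still above 8.
- *A different denominator.* With n = 100, an 80% rate gives 1.96 × √(0.80 × 0.20/100) = 7.8 points, which rounds to 8. The compliance figure may therefore have been computed on 100 instead of 38. That is a guess, and no comparable source was found for the 7.

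**Step 4: sample needed for the stated widths.** n = z² × p(1 − p)/(half-width)².

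- Participation: 3.8416 × 0.2356/0.0049 = 184.7, so 185 eligible patients.
- Compliance: 3.8416 × 0.16/0.0064 = 96.04, so 97 participants.

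**The case against.** The strongest reply is that the number 38 does not depend on these figures. Section 7.3 first gives a practical reason, trying out the procedures in the time available, and offers the precision statements as support. Section 7.1 makes the analysis descriptive. No progression threshold, test or decision rule in the protocol uses ±7 or ±8. Any interval calculated from the data would have the right width whatever section 7.3 says, so it is speculative to claim that the full trial would be planned on falsely narrow intervals. It can also be said that section 7.3 speaks of participation and compliance rates, while sections 4.3 and 4.4 name recruitment and adherence rates, and that the protocol never states that these are the same.

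Most of this stands, and it limits the consequence. The error does not invalidate a sample of 38, and the demonstrable harm is that the protocol overstates its anticipated precision. The choice of interval method can be left to the statistical analysis plan. The match between the rates in section 7.3 and the endpoints is a plausible reading, not an explicit statement. None of this makes the two figures correct: the sentences are complete, give all their inputs, and are not corrected elsewhere in the protocol.

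**Conclusion.** The point holds. On the inputs in section 7.3, the 95% half-widths are about 9.5 points for participation (stated 7) and 12.7 points for compliance (stated 8). Across the Wilson, Agresti-Coull, Jeffreys and exact methods the ranges are roughly 9.3 to 9.9 and 12.1 to 13.9, so the choice of method does not matter to the conclusion.

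The calculation assumes simple binomial sampling, exactly 100 eligible patients, and all 38 participants assessed for compliance with both arms pooled. The last assumption is favourable: withdrawals are not replaced, so any participant without usable adherence data would widen the interval further. The finding concerns a misstatement of precision, not the adequacy of 38 for a feasibility pilot.

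**What to change.** Keep the sample at 38 and correct the two sentences in section 7.3. Suggested text: *If 100 patients are found eligible, a participation rate of 38% will be estimated with a 95% confidence interval of about ±9.5 percentage points. With 38 participants, a compliance rate of 80% will be estimated with a 95% confidence interval of about ±12.7 percentage points (normal approximation).*

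If the sponsor does want ±7 and ±8, the denominators would have to rise to about 185 eligible patients and 97 participants; nothing in the protocol suggests that this is needed for a pilot.

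The cost is two sentences of wording. No patients are added and no procedure changes; the stated precision simply becomes less favourable.
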